#### Study Personnel

Study personnel will consist of graduate students and post-doctoral fellows who are certified physiologists/trainers with ACSM or CSEP, with knowledge in behavioral theory, motivational interviewing, health coaching, and exercise oncology. Each participant in the intervention group will be assigned a movement specialist to lead all behavioral counselling sessions. All personnel will be trained by the Principal Investigator to ensure quality control and fidelity (e.g., manual of operations, provider training [3 × 6 hr sessions], intervention delivery checklists) using the treatment fidelity guidelines for health behavior research recommended by the National Institutes of Health (NIH) Behavior Change Consortium [33].

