#### Randomization

Randomization will be performed by study personnel using a stratified randomization scheme via REDCap. The sequence will be random, permutated blocks of varying sizes, stratified by ADT use (i.e., ADT vs. no ADT). PCS will be assigned in a 1:1 ratio to either the intervention or control group. Randomization codes will be kept in a digital file that is separate from other study records. Only the study co-ordinators and investigators will have access to the randomization codes.

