#### Sample Size

A sample size calculation was performed in G*power based on a multivariate analysis of variance with two intervention levels (i.e., intervention, control) and two dependent variables (i.e., SB and PA). Based on our pilot trial with PCS, we assumed a medium effect size of Cohen’s *d* = 0.50 at the end of the intervention. Based on an alpha of 0.05 and power of 0.80, a total sample size of 100 is required. To account for the expected 20% attrition, a sample of 120 PCS (intervention *n* = 60, control *n* = 60) will be recruited.

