#### Study Conditions

##### Intervention Condition – Fitbit +Behavioral Counselling

The intervention aims to increase daily step counts by ≥3000 steps per day from baseline. The intervention is comprised of five phases which will be delivered through six behavioral counselling sessions (four individual sessions, two group-based webinars). Participants will be provided with a SB workbook and Fitbit Inspire 2 (Fitbit LLC; San Francisco, CA) as an intervention tool to complement the behavioral counselling sessions. The Fitbit Inspire 2 displays steps, distance, calories, sleep/rest time, and provides reminders to move. The Fitbit app syncs wirelessly to computers and smart devices. PCS will be encouraged to wear the device continuously throughout the 12 weeks and to access their SB and activity data at least weekly via the application.

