##### Statistical Analyses

Linear mixed models will be used to model the primary outcome (i.e., SB) and secondary outcomes (i.e., LPA, motivational outcomes from M-PAC, QoL) at the three time points. Fixed effects included in the models will be time (i.e., baseline, 3-month, 6-month post-intervention), group (i.e., intervention, control), and the interaction. A random intercept will be included to account for variance between and within participants. All models will be estimated while adjusting for covariates (e.g., baseline SB, age, treatment type). Sensitivity analyses will be performed to test for informative dropouts.

The same analytic approach will assess subgroup differences of participants which will include several standard demographic (e.g., age, gender), fitness (e.g., baseline PA) and clinical variables (e.g., time since treatment, disease stage) by modeling the changes over time from post-intervention (F_1_: 3-months after baselines) to 6-month follow-up (F_2_: 9-months after baseline). An intention to treat analysis will be conducted based on all available data from PCS randomized regardless of non-adherence during the intervention. Participants with missing data will be included under the missing-at-random assumption of the mixed-model analysis.

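### Counselling clusters intervention participants by movement specialist, but the stated model has only a participant intercept, so a positive specialist correlation would make the standard error of the group difference too small

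*Protocol article*

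**What the plan says.** All references are to the protocol article.

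- **Delivery.** Under Study Personnel: "Each participant in the intervention group will be assigned a movement specialist to lead all behavioral counselling sessions". Under Intervention Condition, the programme consists of "six behavioral counselling sessions (four individual sessions, two group-based webinars"; Table 1 places the webinars in weeks 3 and 9. Under Active Comparison Condition, controls get a short orientation and no further specialist support during the intervention period.
- **Allocation.** Individuals are randomized: "PCS will be assigned in a 1:1 ratio to either the intervention or control group".
- **Model.** Under Statistical Analyses, the fixed effects are time, group and their interaction, with covariates given as examples (baseline sedentary behavior, age, treatment type). The one random term is described so: "A random intercept will be included to account for variance between and within participants".
- **Sample size.** It rests on a "multivariate analysis of variance with two intervention levels (i.e., intervention, control) and two dependent variables (i.e., SB and PA", and "we assumed a medium effect size of Cohen’s *d* = 0.50 at the end of the intervention". The result: "Based on an alpha of 0.05 and power of 0.80, a total sample size of 100 is required". Then: "To account for the expected 20% attrition, a sample of 120 PCS (intervention *n* = 60, control *n* = 60) will be recruited". No ICC or design effect appears.

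**The concern.** The design is partially nested. Intervention participants fall into groups defined by who counsels them, and possibly by who shares their webinar; control participants stand alone. Individual randomization does not remove this, because the grouping arises after randomization and is part of the treatment.

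A participant intercept handles the correlation among repeated measurements on one man. It cannot represent correlation between different men who share a specialist. If some specialists are better than others at reducing sitting time, the model counts that between-specialist variation as independent information from each participant. The interval for the primary comparison is then too narrow, and the nominal 5% test rejects too often. Counselling is what distinguishes the arms and the primary outcome is the behavior being coached, so some specialist variation is plausible.

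**Working it through.** **1. The plan's own figure.** The total of 100 is reproduced approximately by a repeated-measures between-group test with f = d/2 = 0.25, two measures and an assumed correlation of 0.5. The noncentrality is N × 0.25² × 2 / 1.5. At N = 98 this is 8.17 (power 0.808), and at N = 100 it is 8.33 (power 0.816). A one-sided normal comparison of two means at d = 0.50 gives exactly 100. The article does not say which route was used; neither contains a cluster term. Recruiting 120 and losing 20% leaves 120 × 0.8 = 96, or 48 per arm, used below.

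**2. Inputs not in the article.** The number of specialists k, the specialist ICC and the webinar group size are not given. Assumed: k = 4 to 8 and ICC = 0.01 to 0.10, with specialists treated as a random sample.

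**3. Formulas.** The cluster size is m = 48/k. The intervention-arm design effect is DE = 1 + (m − 1) × ICC; the control arm has DE = 1. The ratio of the true to the reported standard error of the difference is R = √((1 + DE)/2). The actual type I error is 2 × (1 − Φ(1.96/R)).

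| ICC | k (m) | DE | R | Type I error |
|---|---|---|---|---|
| 0.01 | 8 (6) | 1.05 | 1.01 | 5.3% |
| 0.01 | 4 (12) | 1.11 | 1.03 | 5.6% |
| 0.05 | 8 (6) | 1.25 | 1.06 | 6.5% |
| 0.05 | 4 (12) | 1.55 | 1.13 | 8.3% |
| 0.10 | 8 (6) | 1.50 | 1.12 | 8.0% |
| 0.10 | 4 (12) | 2.10 | 1.25 | 11.5% |

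Simulating a two-group test that ignores specialist (40,000 runs per case, k = 8 and 4) gives 6.4 to 8.2% at ICC 0.05 and 8.2 to 11.8% at ICC 0.10, in line with the formula.

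R is an inflation factor. With R = 1.129, the reported standard error is 1 − 1/1.129 = 11% too small, not 13%.

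**4. Which specialist term matters.** Baseline is measured before randomization, so a specialist cannot affect it. The group-by-time contrast compares changes from baseline.

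- A specialist intercept that is constant over time cancels from each participant's change. The standard error of the interaction is multiplied by 1.000, so adding such a term corrects nothing.
- An effect present only after baseline does not cancel. Take participant variance 1, an assumed within-person correlation of 0.6 and an added specialist variance of 0.05. The variance of a change is 2 × (1 − 0.6) = 0.8 per participant. The intervention arm gains m × 0.05, which is 0.3 for k = 8 and 0.6 for k = 4. The ratio is √((1.6 + 0.3)/1.6) = 1.09 for k = 8 and √((1.6 + 0.6)/1.6) = 1.17 for k = 4.

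**5. Price of the correction at ICC 0.05.** Approximate Satterthwaite degrees of freedom are (DE + 1)² / (DE²/(k − 1) + 1/47).

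- k = 8: 2.25² / (1.25²/7 + 1/47) = 20.7, t = 2.081. Relative width is 1.061 × 2.081/1.96 = 1.13.
- k = 4: 2.55² / (1.55²/3 + 1/47) = 7.9, t = 2.311. Relative width is 1.129 × 2.311/1.96 = 1.33.

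**The case against.** A reader might infer that the planned standard error is definitely too small and that type I error definitely exceeds 5%. The article does not support that. Both statements need a positive specialist ICC, and every figure for size comes from an assumed ICC and number of specialists. With 8 specialists and ICC 0.01 the error rate is 5.3%, which is close to harmless.

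The article also plans steps that should limit variation between specialists: a manual of operations, three six-hour training sessions, delivery checklists and recognized fidelity guidelines. Content is set by phase and workbook, step goals are common to all, and the primary outcome is device-measured. These steps may well keep the ICC low. They do not show that it is zero.

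The type I figures depend on the null hypothesis meant. If counselling has no effect through any specialist, variation in the delivered effect is zero and this mechanism causes no inflation. The figures apply when specialist effects differ but average zero, and when the inference is meant to reach beyond the staff employed. That is a choice of inference, but a natural one for a programme the Discussion hopes to scale up.

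A separate webinar penalty might also be inferred. Specialists are said to lead all sessions, so webinar groups may simply be nested in specialist. The article does not settle this, and no separate figure is claimed.

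Finally, the article is condensed and an analysis plan, not shown, could add terms. That carries limited weight, because the article does state its random-effects structure, and that structure does not match the delivery it describes.

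**Conclusion.** The point holds conditionally. The clustering in one arm and the single participant intercept are both in the text. The direction follows if outcomes are positively correlated within specialist after baseline. The effect is near negligible at ICC 0.01 and material at 0.05 or more with few specialists; the table covers 48 analysed per arm and 4 to 8 specialists. The documents cannot place the trial within that range. This justifies a modest change to the analysis while the identifiers can still be captured. It does not justify saying that the primary result will be wrong.

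**What to change.** 1. Record the specialist ID and webinar-group ID for every intervention participant; the planned delivery checklists are a convenient place. This costs almost nothing now, but the IDs may not be recoverable later.
2. Pre-name a partially nested mixed model with a specialist effect in the intervention arm that acts only on the post-baseline time points, for example a random specialist-by-post-baseline term. Add a webinar-group term if groups are not nested in specialist. Use Satterthwaite or Kenward-Roger degrees of freedom. An ordinary time-constant specialist intercept will not do, for the reason in step 4 of the working.
3. Make this the primary model if there are enough specialists to estimate the variance; otherwise report it as the named sensitivity analysis beside the primary result. Base that choice on the number of specialists, fixed before outcomes are seen, and not on the estimated variance.

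The cost is a wider interval, at ICC 0.05 about 13% with 8 specialists and about 33% with 4. With 4, more than half of the widening comes from the lost degrees of freedom (2.311/1.96 = 1.18), which is why the sensitivity-analysis route is reasonable when specialists are few.

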#### Study Conditions

##### Intervention Condition – Fitbit +Behavioral Counselling

The intervention aims to increase daily step counts by ≥3000 steps per day from baseline. The intervention is comprised of five phases which will be delivered through six behavioral counselling sessions (four individual sessions, two group-based webinars). Participants will be provided with a SB workbook and Fitbit Inspire 2 (Fitbit LLC; San Francisco, CA) as an intervention tool to complement the behavioral counselling sessions. The Fitbit Inspire 2 displays steps, distance, calories, sleep/rest time, and provides reminders to move. The Fitbit app syncs wirelessly to computers and smart devices. PCS will be encouraged to wear the device continuously throughout the 12 weeks and to access their SB and activity data at least weekly via the application.

The behavioral counselling sessions are grounded in the M-PAC framework [26] and will take place bi-weekly for 30-60 minutes per session (Table 1). Following randomization, PCS will attend an orientation session with study personnel to introduce them to the Zoom environment and Fitbit. PCS will be asked to self-monitor their daily steps through the Fitbit app and an activity log throughout the 12-weeks. Each of the one-on-one behavioral counselling sessions and group webinars will include activities from the SB workbook to support the behavioral counselling discussions. During the first two weeks (Phase 0), participants will engage in self-monitoring to obtain a baseline step count, which will provide opportunities for tailored goal setting throughout the subsequent phases. Phase I (weeks 3-4) will include a group webinar focusing on reflective processes (i.e., perceived capability and opportunity, instrumental attitudes, and affective judgments) and information about the benefits of reducing SB. PCS will be encouraged to replace SB with LPA by increasing their daily steps by 1000 steps/day above their baseline levels. Phase II (weeks 5-6) and Phase III (weeks 7-8) will focus on behavioral regulation (Phase II: goal setting and action planning; Phase III: coping planning and social support) through one-on-one sessions during each phase (six sessions in total). PCS will be encouraged to increase their daily step counts by 2000 steps/day and 3000 steps/day above their baseline level during Phase II and Phase III, respectively. Phase IV (weeks 9-10) will focus on reflexive processes (i.e., self-regulation consolidation, habit) through a group webinar and a one-on-one session. Phase V (weeks 11-12) will include a final one-on-one booster session to address individual challenges or revisit previous behavioral support topics as needed. Participants will be encouraged to maintain their new daily step count (i.e., 3000 steps/day above baseline) throughout Phases IV and V (see Table 1).

**Table 1 Tab1:** Delivery of the intervention and behavioral counselling components

Phase (Weeks)	Description				M-PAC Framework [26] Construct	Description of Behavioral Strategies
	Session Type		Focus	Movement Goal^**a**^		
	1-on-1	Group				
Phase 0 (Weeks 1-2)	N/A	N/A	Self-monitoring typical daily sitting time and step counts	No change in activity levels	N/A	N/A
Phase I (Weeks 3-4)		Week 3	Increasing low intensity, incidental movement	↑1000 steps/day	Reflective Processes • Perceived capability • Perceived opportunity • Instrumental attitudes • Affective judgments	• Benefits of reducing sitting time and increasing movement for health and clinical outcomes • How to make activity enjoyable
Phase II (Weeks 5-6)	Week 5		Continuing to increase daily steps and interrupt sitting time	↑2000 steps/day	Behavioral Regulations • Goal setting • Action planning	• Setting challenging, yet achievable goals • Creating plans to increase step counts
Phase III (Weeks 7-8)	Week 7		Increasing activity to longer sessions of activity	↑3000 steps/day	Behavioral Regulations • Coping planning • Social support	• Strategies to overcome barriers to daily movement • How to obtain social support from others
Phase IV (Weeks 9-10)	Week 10	Week 9	Consolidation: combining self-regulatory strategies learned in previous phases	Maintain 3000 steps/day	Reflexive Processes • Self-regulation consolidation • Habit	• Tagging movement behaviors to existing schedule • Utilizing environmental cues • Developing rewards
Phase V (Weeks 11-12)	Week 11		Maintenance: combining self-regulatory strategies learned in previous phases	Maintain 3000 steps/day	Booster Session	• Individual challenges and barriers to setting goals • Revisit previous topics as needed

^a^All goals indicate a change from the participant’s baseline steps identified in Phase 0

#### Active Comparison Condition: Fitbit-only Control

Participants will receive a Fitbit Inspire 2, the Canadian 24-hour Movement Guidelines [34], and a list of free public health resources about maintaining a healthy lifestyle (e.g., Canada’s ParticipACTION app). Following a brief orientation session on how to use the Fitbit and overview of the provided public health resources, the Fitbit-only comparator condition will not receive additional behavioral support from the movement specialists for the intervention period.

### Data Collection

Data will be collected at baseline (T_1_), post-intervention (F_1_), and 6 months post-intervention (F_2_). Participants will complete an electronic questionnaire on REDCap (20 minutes) and will be mailed an activPAL inclinometer. PCS will meet with a movement specialist blinded to group allocation through videoconferencing (i.e., Zoom) to ensure proper fitting of the activPAL, and to complete the physical function test (30 minutes). Study personnel completing data collection will be blinded to group allocation. A summary of outcomes and data collection time points is shown in Table 2. Participants will receive a $60 honoraria for study completion ($20 for each completed assessment; T_1_, F_1_, F_2_).

**Table 2 Tab2:** Summary of outcome measures

Item	Instrument	Study Period				
		Enrollment	Baseline Assessment/ Allocation	Post-Allocation 12-week Intervention	Post-Intervention	6 months Post- Intervention
		T_0_	T_1_	T_2_	F_1_	F_2_
Eligibility Screen	N/A	X				
Informed Consent	N/A	X				
Allocation	N/A		X			
1. **Primary Outcomes**						
Objectively-measured Sedentary Behavior	ActivPAL		X		X	X
2. **Secondary Outcomes**						
Self-reported Domain-specific Sedentary Behavior	LASA Sedentary Behavior Questionnaire		X		X	X
Objectively-measured Physical Activity	ActivPAL		X		X	X
Self-reported Physical Activity	GLTEQ		X		X	X
Motivational Processes	Standard measures from the M-PAC (15 items)		X		X	X
Mental Health	HADS		X		X	X
Quality of Life	FACT-General, FACT-Fatigue, SF-12		X		X	X
Health and Disability	WHODAS 2.0		X		X	X
Physical Function	30-second chair stand		X		X	X
Internet & Technology Use	eHEALS		X			
Patient Satisfaction	30 items				X	
3. **Covariates**						
Sociodemographics	6 items		X			
Medical History	10 items		X			
**Group Allocation**						
Intervention				X		
Fitbit-Only Control				X		

*Abbreviations*: *LASA* Longitudinal Aging Study Amsterdam, *GLTEQ* Godin Leisure Time Exercise Questionnaire, *M-PAC* Multi-Process Action Control, *HADS* Hospital Anxiety and Depression Scale, *FACT-General* Functional Assessment of Cancer Therapy – General, *FACT-Fatigue* Functional Assessment of Cancer Therapy –Fatigue, *SF-12* Short Form-12, *WHODAS 2.0* World Health Organization Disability Assessment Schedule 2.0, *eHEALS* eHealth Literacy Scale

#### Primary Outcome

##### Sedentary Behavior

Objectively-measured SB will be assessed with an activPAL inclinometer (PAL Technologies, Ltd; Glasgow, UK), which quantifies free-living SB and ambulatory activities. The inclinometer is a small, lightweight device secured to the anterior midline of the right thigh using Tegaderm dressing (3M Medical, USA). It provides time spent in sitting, lying, standing and stepping, as well as estimates energy expenditure expressed as metabolic equivalents (METs) [35]. It has been shown to be a valid and reliable measure compared to direct observation (R^2^ = 0.94) [36], and these devices have been used in cancer populations [11, 37]. Participants will be mailed the inclinometer to wear for seven consecutive days. A wear log will be used to record sleep and wake times, daytime naps, and periods of device removal.

Self-reported SB will be assessed with the Longitudinal Aging Study Amsterdam (LASA) Sedentary Behavior Questionnaire [38]. The LASA measures self-reported sedentary time in ten sitting behaviors on an average weekday and weekend day including occupational, transportation, and leisure-time sitting behaviors (hours and minutes). The questionnaire has a test-retest reliability of 0.71 (95% CI 0.57-0.81) and has been used in older adults [38–41].

### Secondary Outcomes

#### Physical Activity

Self-reported leisure-time PA will be assessed using the Godin Leisure-Time Exercise Questionnaire (GLTEQ) [42, 43]. Participants will report the number of times per week spent in light, moderate, and vigorous leisure-time PA, which will be used to calculate a total leisure activity score. The GLTEQ has been validated and frequently used to assess PA in cancer populations [42, 43]. The GLTEQ will be modified to remove the stipulation to only consider activity completed in bouts of 10 minutes in line with the current PA guidelines for cancer survivors [9]. The GLETQ has good internal consistency with reliability coefficients of 0.83 and 0.85 [42]. Objectively-measured PA will be assessed with the activPALs. A cadence <100 steps/minute will be considered LPA [44, 45].

#### Motivational Processes

Standard M-PAC questionnaires will be modified to assess participants’ reflective (i.e., instrumental and affective attitudes, perceived capability and opportunity), regulatory (e.g., self-monitoring, goal setting, action and coping planning), and reflexive processes (e.g., habit) related to reducing SB. A 7-point Likert scale (strongly disagree to strongly agree) will be used to assess the extent to which participants believe replacing SB with LPA will be exciting/enjoyable/pleasant and wise/beneficial/pleasant to assess *affective* and *instrumental attitudes*, respectively [46]. *Perceived capability* and *opportunity* will be assessed through six statements regarding confidence and control over engaging in LPA to replace SB (e.g., perceived capability: “I possess the skills to replace sedentary time with light PA regularly over the next 12 weeks if I wanted to”; perceived opportunity: “If I really wanted to replace sedentary time with light PA regularly over the next 12 weeks, I would have the chance to do so”) [47, 48]. *Regulatory* and *reflexive* processes will be rated on a 5-point Likert scale (strongly disagree to strongly agree) [49–51]. Example statements include: “I kept track of my daily light PA and sedentary time in a diary or log over the last month” (self-monitoring); “I made plans regarding what to do if something interfered with my plan to replace sedentary time with light PA last month” (coping planning); “Reducing sedentary time to be more active is something I do automatically” (habit). *Intentions* to replace light PA will be assessed using the following prompt: “I intend to engage in regular light PA _________ times per week/weekday/weekend day during the next 12 weeks.”

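### The example self-monitoring item names only a diary or log, so it may under-count Fitbit-app tracking by controls at post-intervention; separately, 'pleasant' is listed under both attitude constructs

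*Protocol article*

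**What the plan says.** The Motivational Processes section of the Protocol article says that standard M-PAC questionnaires will be adapted to reducing sedentary behavior. Regulatory and reflexive processes are rated on a five-point agreement scale. The text introduces sample items with "Example statements include", and the one for self-monitoring is "I kept track of my daily light PA and sedentary time in a diary or log over the last month".

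The description of the intervention arm states: "PCS will be asked to self-monitor their daily steps through the Fitbit app and an activity log throughout the 12-weeks". The description of the control arm states: "Participants will receive a Fitbit Inspire 2, the Canadian 24-hour Movement Guidelines", together with a list of public resources. Controls are also shown how to use the device ("Following a brief orientation session on how to use the Fitbit"). No activity log is mentioned for them.

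For attitudes, the same section gives the descriptors "exciting/enjoyable/pleasant and wise/beneficial/pleasant", assigned to affective and instrumental attitude in that order.

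The last paragraph of the Background makes motivational outcomes against the Fitbit-only control a secondary objective. The Statistical Analyses section models them with time, group and their interaction.

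**The concern.** The trial is meant to isolate what counselling adds to a Fitbit that both arms have. A self-monitoring measure should therefore give the same credit to the same amount of tracking in either arm. The sample item names a tool described for one arm only and leaves out the tool common to both. A control who checks the app every day and reads the item literally has reason to score low. An intervention participant who tracks equally often, but also writes in the log, has reason to score higher. Part of any F1 difference in self-monitoring could then reflect the method of tracking rather than its amount, and counselling would be credited with too large an effect on that one process.

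The attitude descriptors raise a different question. 'Pleasant' sits naturally with exciting and enjoyable, not with wise and beneficial. The Background gives the two attitudes separate roles: instrumental attitude in forming an intention, affective attitude in enacting it. A shared adjective makes it harder to tell them apart.

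**Working it through.** The protocol gives no figure on this point to reproduce, so the check sets the texts side by side and adds one item count.

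**Tracking tools by arm**
- Intervention: Fitbit app and activity log, for all 12 weeks (Intervention Condition).
- Control: Fitbit and orientation, no log mentioned (Active Comparison Condition).
- Named in the item: diary or log only.
- The activPAL wear log, described under the primary outcome, covers sleep, naps and device removal. It does not cover light activity or sitting, so it gives controls no literal ground for agreeing.

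**Recall window by assessment**
- T1: assessed before randomization, so neither arm has yet been given the trial's tracking tools. The mechanism is absent.
- F1: immediately after week 12, so the last month is roughly weeks 9 to 12. The log task is still in force and the mechanism can operate.
- F2: 9 months from baseline, so the last month runs from about month 8 to month 9. The log task ended at week 12, about month 3, which is some 8 − 3 = 5 months before that window opens. The article gives no reason to expect the mechanism here.

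**What the log records**
- The assigned log covers daily steps; the item asks about light activity and sedentary time.
- Table 1 mentions self-monitoring of sitting time only in Phase 0 (weeks 1-2), outside the F1 window. Keeping the log makes agreement easier but does not guarantee it.

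**How many items might measure self-monitoring**
- Table 2 gives 15 M-PAC items in total. Motivational Processes gives six statements for capability and opportunity.
- Assumption, not stated in the article: each attitude adjective is one item, giving 3 affective + 3 instrumental = 6.
- Items left: 15 − 6 − 6 = 3, to cover self-monitoring, goal setting, action planning, coping planning, habit and intention (six constructs). One item each would need 6 + 6 + 6 = 18.
- On that assumption self-monitoring rests on one or very few items, leaving little room for other items to dilute the problem. The article does not give the actual number.

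**Attitude overlap**
- One of three listed descriptors is shared. If each is one equally weighted item (again an assumption), 1/3 = 33% of the instrumental score comes from an affective adjective.
- The descriptors are the same in both arms, so the overlap has no arm-specific component.

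**The case against.** The strongest reply is that the item is offered as an example. A journal article normally leaves the full item list to the complete protocol, and other self-monitoring items may cover device tracking. This stands: the text does not show that the whole scale is restricted to diaries and logs. The item count makes a long self-monitoring scale unlikely, but only under the one-item-per-adjective assumption.

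Second, the log is a delivered component and self-monitoring is a process the intervention targets, so some of the contrast is a genuine effect. This also stands. The problem is confined to app-only tracking by controls that the item may miss.

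Third, a control may regard the app record as a log, and a five-point scale allows partial agreement. So it cannot be said that controls have to disagree, nor, given that the assigned log concerns steps, that intervention participants agree merely by following instructions. That controls keep no log is itself inferred from the article's silence.

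Fourth, the repeated adjective may be a slip in the article rather than in the fielded questionnaire. That is possible, and it is a reason to check.

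A reader might infer that the measure biases the motivational objective as a whole. The documents do not support that. Nothing here touches perceived capability, perceived opportunity, coping planning, habit or intention. The log mechanism belongs to F1, and the shared adjective is common to both arms.

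**Conclusion.** The point holds in a narrow form and is minor. If the example item is fielded as written, it may under-count app-based self-monitoring by controls and widen the self-monitoring contrast at F1. The direction is plausible; the size is unknown. A reader might try to express it in percentage points from assumed shares of trackers in each arm. The article supplies no such shares, and a yes/no share is not what the planned linear mixed model would estimate from a five-point score.

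The conclusion rests on two assumptions: that respondents take diary or log in its ordinary sense, and that few other items dilute this one. Separately, listing 'pleasant' under both attitudes weakens the distinction between the subscales without by itself biasing the comparison between arms.

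**What to change.** Reword the self-monitoring item so that it counts any tracking open to both arms (the Fitbit app, another device, a diary or a log), and use that wording at T1, F1 and F2. Check the fielded instrumental attitude list and, if 'pleasant' is there, replace it with an instrumental adjective such as 'useful'. The protocol already plans to modify these questionnaires, so this is a small REDCap edit. The cost is slightly less comparability with earlier uses of the item.

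If data collection has begun, score instrumental attitude from wise and beneficial only. Add the reworded item at the remaining assessments and compare arms on it at F1 and F2 without a baseline value. Interpret the diary/log item at F1 as partly reflecting compliance with the assigned log. The further cost is that the late item cannot be analysed with the three-time-point, baseline-adjusted model planned for the other outcomes. Randomization still supports the comparison between arms, with some loss of precision.
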